### Data collection and management

Patients’ demographic data, main diagnosis, comorbidities, assigned crystalloids, general vital signs, SOFA scores, APACHE II, infection indices, and indices of multi-organ function including renal function, respiratory function, cardiac function, etc. at the time of enrolment will be collected as baseline data. Clinical information including infection indices (white blood cell count, procalcitonin, etc.), organ function indices (renal function (creatinine, urea nitrogen, cystatin C, urine volumes, etc.), respiratory function (PO_2_/FiO_2_, ventilation situation, etc.), hepatic function (total bilirubin, etc.), and indices of internal environment (blood gas analysis) will be detected during the first 5 days in ICU, and treatments such as vasopressors, mechanical ventilation, RRT, and electrolyte supplement will be recorded. These data and infused volumes of the assigned fluids will be collected for at least 5 days or until ICU discharge. ICU stay days, vasopressor days, RRT days, and ventilation days will be counted during 28 days after enrolment. These data will be collected to assess and analyze primary and secondary outcomes. Besides, patients’ blood and urine samples within the first 3 days after enrolment will be collected and stored for testing possible biomarkers for identifying AKI at an early stage.

Patients’ information and clinical data will be collected from the Hospital Information System (HIS) of the hospitals involved in this study and recorded in the Case Report Format (CRF) by the trial manager or trained personnel. An electronic password-protected excel, which will be applied for statistical analysis, will be created to summarize the data of all participants. All the data will be accessed by only investigators and authorized personnel to monitor the completeness and authenticity of the table. The confidentiality is secured and all the data will be preserved for the purpose of a secondary analysis or investigations by the investigators. To protect patients’ privacy, their names will not appear on the CRF table. Every participant will only be recognized by their study ID.

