**Methods/design:**

The investigators designed a pragmatic, multi-center parallel controlled trial recruiting 312 patients who are diagnosed with sepsis/septic shock in the intensive care unit (ICU) and will be assigned with either acetate Ringer’s solution or saline in the corresponding month. Patients with an end-stage renal disease (ESRD) or who need renal replacement therapy (RRT) prior to or at the time of enrolment are excluded. Enrolled patients will be regarded as with mild, moderate, or severe sepsis on the basis of the severity of their illness and will be divided into subgroups according to their initial renal function and various intravenous infusion volumes when being analyzed. The primary outcome is major adverse kidney events within 28 days (MAKE28), including the composite of in-hospital death, receipt of new renal replacement therapy, or persistent renal dysfunction. Secondary outcomes include 28-day mortality, internal environment disturbance, incidence and duration of vasoactive drug treatment, duration of mechanical ventilation, duration of RRT, and ICU and hospital length of stay.

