### Study outcomes

The primary outcome is MAKE28 (major adverse kidney events) [22]—a composite of in-hospital death, new renal replacement therapy, or persistent renal dysfunction (defined by an estimate glomerular filtration rate (eGFR) lower than 60 ml/min/1.73 m^2^ for at least 3 months [23, 24]) within 28 observational days.

Secondary outcomes will include:
The occurance of AKI which is diagnosed according to the Kidney Disease Improving Global Outcomes (KDIGO) criteria [25];Twenty-eight day mortality;Electrolyte disturbance, including hypernatremia, hyperchloremia, and hyperkalemia as well as hyponatremia, hypochloremia, and hypokalemia;Changes of renal functions based on the biomarkers measured from the participants’ plasma and urine samples collected in the first 3 days after enrolment; andOther clinical outcomes: ICU stay days, ventilator days, vasopressor days, and RRT days.

Pre-specified subgroups for primary and secondary outcome analyses will mainly include:
With or without acute kidney injury (no AKI, AKI stage 1, AKI stage 2, or AKI stage 3);With or without septic shock;Low versus high severity of sepsis: mild, moderate, and severe (classified by SOFA scores or Acute Physiology and Chronic Health Evaluation II (APACHE II) scores); andIntravenous infused volumes of the assigned crystalloids.

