### Sample size and statistical power

The sample size was calculated based on the occurrence of MAKE30 on septic patients, which was around 35% [17]. With a noninferiority limit of 1.5%, a total of 312 study participants (156 in each group) would result in a power of at least 80% with a one-sided type-1 error rate (*α*) of 2.5%, allowing a 20% withdrawal rate in each group.

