### Statistical analysis

Measurement data that conform to normal distribution will be described as mean ± SD, while ones that do not will be reported as the median and interquartile range (IQR). Count data will be notified as frequencies and proportions. As for single-factor analysis, the difference of measurement data will be compared with *T* test between two groups or with one-way analysis of variance among three groups. Chi-square test and Fisher’s exact test will be used for rate comparison. As for multi-factor analysis, variables which showed a significant difference in the univariate analysis will be processed by logistic multivariate regression analysis. Multiple linear regression analysis will be used to demonstrate the linear relationship between variables. *P* value < 0.05 will be considered statistically significant. SPSS 24.0 will be used to complete data processing and statistical analysis.

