### Additional secondary analysis

Statistical methods mentioned in the statistical analysis will be applied according to the characteristics and distribution of the data.
Compare the secondary outcome between the two groups;Subgroup analysis will include:
Septic shock (yes/no)Stage of AKI on the enrolment day (no AKI, AKI, chronic kidney disease without receiving RRT regularly)intravenous volumes of the assigned crystalloidsThe APACHE II scores and SOFA scores at the day of enrolmentReceipt of mechanical ventilation (yes/no) and ventilation daysReceipt of vasopressor (yes/no), vasopressor category, and max dosesReceipt of RRT (yes/no) and RRT daysMain diagnosis at the time of admission to hospital (nervou s system disease, respiratory system disease, cardiovascular system disease, digestive system disease, urinary system disease, hematologic system disease, endocrine system disease)Complications (hypertension, diabetes, coronary heart disease, etc.)

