### Handling of missing data

Of the primary outcome, data of the rate of AKI and the percentage of new receipt of RRT are not supposed to be missing for any patients. Nevertheless, some data of renal function may be missing due to protocol executive errors or record-keeping errors. Mean completer, hot deck imputation, and filling manually will be taken to minimize the effects of these missing data as much as possible. For example, if the renal function values near the missing value are in the normal range or have the same trend, the missing data will be averaged or filled with proximity. Patients without a serum creatinine measurement between enrolment and hospital discharge who survive and do not receive new RRT will be considered as not having experienced MAKE. If the patients or authorized agents give up treatment due to little chance to survive predicted by clinicians, their outcome is considered to be death. Besides, in-hospital mortality may be missing due to patients or authorized agents giving up treatment or other unpredictable accidents when the illness is not that severe. Data may also be missing due to severe adverse events (SAEs) or patients quitting the trial. Under these circumstances, an intention-to-treat analysis will be conducted to deal with the missing data. Of other outcomes, deletion will be considered if the missing data is too large to fill. Indices with complete data after conservative imputation will be included in the statistical analysis.

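### ICU, ventilator, vasopressor and RRT days are compared as raw 28-day counts with no rule for death, so they favour the arm with more or earlier deaths if mortality or its timing differs

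*Protocol article*

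**What the plan says.** Study outcomes and Table 1 of the protocol article list ICU stay, ventilator, vasopressor and RRT days among the secondary outcomes. Data collection and management fixes how they are measured: "ICU stay days, vasopressor days, RRT days, and ventilation days will be counted during 28 days after enrolment". The abstract also presents such outcomes as durations, with hospital stay added: "duration of mechanical ventilation, duration of RRT, and ICU and hospital length of stay".

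Additional secondary analysis plans a between-group comparison of the secondary outcomes and gives the method as follows: "Statistical methods mentioned in the statistical analysis will be applied according to the characteristics and distribution of the data". The section it points to, Statistical analysis, says that "the difference of measurement data will be compared with *T* test between two groups". It names no rank test and no time-to-event method.

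Death enters the plan in two other places. The primary outcome MAKE28 is "a composite of in-hospital death, new renal replacement therapy, or persistent renal dysfunction", and 28-day mortality is a secondary outcome. Handling of missing data does not mention day counts cut short by death. Its general rule is: "Of other outcomes, deletion will be considered if the missing data is too large to fill".

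**The concern.** Death ends ventilation, vasopressors, RRT and the ICU stay. In a raw count, a patient who dies on day 2 contributes at most about two days, the same as a patient who recovers by day 2. The measure cannot tell the worst result from one of the best. If one fluid leads to more or earlier deaths, its mean support time falls for that reason alone, and four secondary outcomes drift in its favour.

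This is not a detail left to an unseen analysis plan. The article itself states the variable, the window and the family of tests, and an analysis plan that followed it would carry the problem forward. A rank test on the same raw counts would not help, because early deaths would still rank as short durations.

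**Working it through.** The documents give no figure for these outcomes, so there is none to reproduce. They also give no mortality rate. The nearest is the planning rate for the whole composite, "the occurrence of MAKE30 on septic patients, which was around 35" per cent, and the share of it due to death is not stated. Mortality, death timing and support duration below are therefore assumptions.

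**Inputs**
- From Sample size and statistical power: "a total of 312 study participants (156 in each group) would result in a power of at least 80% with a one-sided type-1 error rate", hence 156 per arm.
- Assumed: the same latent ventilation need in both arms (lognormal, median 8 days, log-SD 0.7, capped at 28); every patient ventilated; death times among those who die exponential with mean 7 days, capped at 28.
- Raw days = min(need, death time, 28). Free days = 28 − need in survivors and 0 in patients who die by day 28.

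**Step 1, the mechanism.** In simulation, survivors average 9.8 raw days and those who die average 4.7, a gap of 5.1 days.

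**Step 2, arm means.** With mortality p:
- mean raw days = (1 − p) × 9.8 + p × 4.7
- mean free days = (1 − p) × (28 − 9.8) = (1 − p) × 18.2

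| Mortality | Raw days | Free days |
|---|---|---|
| 25% | 0.75 × 9.8 + 0.25 × 4.7 = 8.5 | 0.75 × 18.2 = 13.65 |
| 30% | 0.70 × 9.8 + 0.30 × 4.7 = 8.3 | 0.70 × 18.2 = 12.74 |
| 35% | 0.65 × 9.8 + 0.35 × 4.7 = 8.0 | 0.65 × 18.2 = 11.83 |
| 40% | 0.60 × 9.8 + 0.40 × 4.7 = 7.8 | 0.60 × 18.2 = 10.92 |

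**Step 3, differences, deadlier arm minus the other.** Raw: −(mortality gap) × 5.1. Free: −(mortality gap) × 18.2.
- 35% vs 25%: raw −0.10 × 5.1 = −0.51; free −0.10 × 18.2 = −1.82.
- 30% vs 25%: raw −0.05 × 5.1 = −0.26; free −0.05 × 18.2 = −0.91.
- 28% vs 25%: raw −0.03 × 5.1 = −0.15.
- Equal mortality and timing: raw 0.

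Fewer raw days look like a benefit; fewer free days are a harm. With log-SD 0.8 instead of 0.7, the 35% vs 25% case gives raw 8.26 vs 8.83 (−0.57) and free 11.57 vs 13.33 (−1.76). The result does not hinge on that choice.

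**Step 4, timing alone.** With log-SD 0.8 and 25% mortality in both arms, a mean time to death of 4 vs 7 days gives a raw difference of −0.34, and 4 vs 10 days gives −0.61. Free days show about 0 in both cases.

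**Step 5, not every patient supported.** At 35% vs 25%:
- half of patients ventilated: 0.50 × (−0.51) = about −0.25 days;
- 15% supported, as might hold for RRT: 0.15 × (−0.51) = −0.08 days;
- short support (median 3 days, 60% of patients), by simulation: −0.07 days.

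**Step 6, how often a trial of this size would mislead.** With 156 per arm, everyone ventilated and 35% vs 25%, the deadlier arm has the shorter mean in about 76% of simulated trials. A two-sided t test at 0.05 significantly favours it in about 11%, against 2.5% by chance. At 30% vs 25% that figure is about 5%.

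**The case against.** Three stronger readings are tempting, and the documents support none of them.

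- *A reader might infer that the trial expects mortality to differ.* The abstract's hypothesis concerns renal outcomes. The Background reports no mortality difference in the four-ICU trial and no significant one in the five-ICU trial. Death is a component of MAKE28, but that does not predict a gap.
- *A reader might say that the raw count reverses the sign of the effect.* In these calculations the true effect on support need is zero, so no duration effect exists to be reversed. The 1.8-day loss of free days comes entirely from death. Free days answer a different question from duration.
- *A reader might expect a false claim of benefit to be likely.* About 11% is an excess over chance, but it needs a 10-point mortality gap with every patient ventilated. A figure as high as 39% (two-sided rejections) appears only with 20% vs 35% mortality combined with earlier death (mean 4 vs 7 days).

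The half-day figure is also modelled for ventilation only and should not be carried over to vasopressor, RRT or ICU days. In addition, 28-day mortality is reported as its own outcome, so an attentive reader would see an excess of deaths. That limits misreading but does not remove the bias. These points restrict the size and likelihood of the problem. They do not supply the missing rule for death, which no section provides.

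**Conclusion.** The point holds in conditional form. The four outcomes are fixed as raw counts and compared between arms without regard to death. The direction of the resulting bias is known: with equal support need, it favours the arm with more or earlier deaths. Its size is not known from the documents. Under the stated assumptions it is about 0.5 ventilator days at 35% vs 25% mortality and about 0.3 days at 30% vs 25%, less where the support is used by fewer patients or for shorter periods, and about zero if mortality and its timing do not differ. It concerns secondary outcomes only; the MAKE28 and 28-day mortality results do not depend on it. It is worth correcting because the correction is cheap, not because the trial's main conclusion is at risk.

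**What to change.** By amendment, make the between-arm comparison on days alive and free of ICU, ventilator, vasopressor and RRT to day 28, with death by day 28 scored 0. Use a rank test or a proportional-odds model, and present 28-day mortality beside each result. Keep the registered raw day counts as descriptive results, shown separately for survivors and non-survivors; they need not be deleted.

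Costs:
- The day counts and vital status are already collected, so no new measurement is needed. Handling of missing data does expect in-hospital mortality to be missing for some patients who give up treatment, so day-28 vital status must be actively obtained for them.
- The outcomes are registered, recruitment has begun and the trial is open-label. The amendment must be dated and justified, and should be made without reference to results by arm.
- Free days mix death with duration, do not isolate an effect on duration and, when death scores 0, do not register earlier death alone. The report should say so.

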### Risk evaluation and adverse events

The trial is considered to pose a low risk. Firstly, saline and acetate Ringer’s solution have already been widely used in the clinical practice of ICUs of the above hospitals. Secondly, it still remains controversial which fluid (saline or balanced crystalloid solution) is better for septic patients. Thirdly, clinicians are allowed to make clinical judgments and choose the other crystalloid for a specific patient if they think the assigned one may increase the risk of poor prognosis. Certainly, data of these patients will not be included in the final analysis. Therefore, the adverse events (AEs) of this trial may be minimal.

Still, during the entire observational 28 days from the beginning of the trial, possible AEs will be assessed and recorded in the CRF table. Investigators will evaluate the relationship between the events and our intervention by clinical judgment, and the events will be graded as mild, moderate, and severe. SAEs should be considered if unexpected clinically significant critically ill diseases which may be resulted from fluid intervention happen. AEs, especially SAEs, must be reported to DSMB and followed until they are solved. At the end of the trial, AEs and their relationship to the study will be documented in a table and submitted.

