### Study fluid distribution and logistics

Acetate Ringer's soution and saline administered in this trial both have different volume sizes of 250 ml and 500 ml. Components of these two crystalloids are presented (Table 2). The study is an open-label study; thus, the exact solution used is known to investigators, clinicians, and patients. Since the study is non-blind and two fluids used in this study have already been widely applied in the daily care of patients in the above ICUs, there are no problems of logistics.

**Table 2 Tab2:** Components of two crystalloids administered in the trial

Components (mmol/L)	Acetate Ringer’s solution	0.9% saline
Na	140	154
K	4	-
Mg	1	-
Ca	1.5	-
Cl	115	154
Glucose (%)	1	-
Buffer system	Acetate 25	-
Osmotic concentration (mOsmol/kg)	304	286

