### Primary analysis

The primary analysis will be an intention-to-treat comparison of the primary outcome of MAKE28 between the saline and acetate Ringer’s solution. A generalized linear mixed-effects model will be used including fixed effects (sex, age, body mass index, group assignment, principal diagnosis, crystalloids received prior to ICU, SOFA score, APACHE II score, mechanical ventilation status, vasopressor usage, etc.) and random effects. It is aimed to describe patients’ baseline characteristics and eliminate confounding factors.

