## Summary/discussion

Fluid resuscitation is the mainstream for the treatment of patients with sepsis/septic shock, and all the guidelines recommend crystalloids as the first choice. Normal saline, a very common crystalloid, poses hyperchloremia and probably worsens AKI which is always complicated by sepsis [26]. However, it is unknown if saline can be safely used in septic patients. Recent studies demonstrated different conclusions in kidney outcomes between saline and balanced solutions in overall critically ill patients [15–17], but showed a significant difference in septic patients by subgroup analysis [16, 17]. This enlightens us to study on a possible dose-response relationship in a high-risk population. Thus, we hypothesize that the harmful effects of saline are associated with the initial kidney function and infused volume of fluids. To confirm this hypothesis, we will carry out this study. As sepsis or septic shock is one of the most typical problems requiring large volume of fluids, this also makes it clinically practically significant to investigate. To our knowledge, this study will be the first to focus on septic patients and compare the effects on outcome between balanced crystalloid solution and saline. In light of this study, a particular comparison will be conducted between acetate Ringer’s solution and saline. Firstly, the patients recruited will be confined to septic/septic shock. Therefore, the conclusions will be applied specifically in septic population. Secondly, the analysis of the association between the due solution and outcome, especially the development of AKI, will be more in details. The infused volume and the baseline renal function will both be taken into consideration. If this trial demonstrates that balanced crystalloid solution or saline shows a priority over the other, it can provide an evidence for the guideline on fluid resuscitation for septic/septic shock. Therefore, the results of this study may be instructive and meaningful.

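### Patients given the other crystalloid are dropped from the final analysis, which contradicts the intention-to-treat primary analysis and can bias MAKE28 if switching or switched-patient risk differs by arm

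*Protocol article*

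**What the plan says.** Under Primary analysis, the article states: "The primary analysis will be an intention-to-treat comparison of the primary outcome of MAKE28". Under Handling of missing data it invokes the same principle for patients who leave the trial or have data missing after a serious event: "an intention-to-treat analysis will be conducted to deal with the missing data".

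Under Risk evaluation and adverse events, clinicians may "choose the other crystalloid for a specific patient if they think the assigned one may increase the risk of poor prognosis". The text then says: "Certainly, data of these patients will not be included in the final analysis". Nothing confines that sentence to a per-protocol or sensitivity set.

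Two other statements bear on how the rule would work. The trial is open-label, so "the exact solution used is known to investigators, clinicians, and patients". The Summary/discussion sets out the investigators' expectation: "we hypothesize that the harmful effects of saline are associated with the initial kidney function and infused volume of fluids".

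**The concern.** Intention-to-treat keeps each patient in the arm assigned, whatever fluid was given. The exclusion rule removes patients because of the fluid given. If the rule is followed, the analysis called intention-to-treat becomes an analysis of patients who stayed on their assigned fluid.

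The selection is not neutral by design. The trigger is a judgement that the assigned fluid may harm this patient's prognosis, made by someone who knows which fluid it is, in a trial whose own hypothesis is that one of the two fluids is harmful. Unequal switching between arms, or switched patients whose MAKE28 risk differs from the rest, is therefore plausible. Either would shift the primary comparison without any true effect. The same loss would carry into the main secondary analysis by infused volume and initial renal function, because it uses the same outcome.

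**Working it through.** **Textual check.** Take a patient assigned to saline whose clinician chooses acetate Ringer's. Under Primary analysis this patient counts in the saline arm. Under Risk evaluation and adverse events this patient is not analysed. No wording elsewhere in the article reconciles the two. The eligibility criteria contain no such exclusion, so it cannot be read as an entry criterion.

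**Inputs for an illustration.**
- Event rate 35%, from Sample size and statistical power. It is a MAKE30 rate in septic patients, applied here to MAKE28.
- 156 patients per arm and a noninferiority limit of 1.5%, from the same section. The limit is read as an absolute difference and used only as a yardstick.
- Share switched, s, and MAKE28 risk in switched patients, r. The article gives neither, so both are assumptions.
- No true effect, and the switch itself does not alter outcome.

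The article has no figure of its own for switching, so there is none to reproduce.

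**Formula.** Rate among those retained in an arm = (0.35 − s·r)/(1 − s). Shift = that rate − 0.35.

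**Saline-only switching, s = 10%.**
- r = 50%: (0.35 − 0.05)/0.90 = 0.333, shift −1.7 points
- r = 60%: (0.35 − 0.06)/0.90 = 0.322, shift −2.8 points
- r = 70%: (0.35 − 0.07)/0.90 = 0.311, shift −3.9 points

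At r = 60%, s = 5% gives 0.32/0.95 = 0.337 (−1.3 points) and s = 15% gives 0.26/0.85 = 0.306 (−4.4 points).

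**Switching in both arms.** Spurious difference, acetate Ringer's minus saline, in points:

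| Switched, saline / acetate Ringer's | r = 35% | r = 50% | r = 60% | r = 70% |
|---|---|---|---|---|
| 10% / 0% | 0 | 1.7 | 2.8 | 3.9 |
| 10% / 5% | 0 | 0.9 | 1.5 | 2.0 |
| 10% / 10% | 0 | 0 | 0 | 0 |
| 20% / 5% | 0 | 3.0 | 4.9 | 6.9 |

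Exchanging the two arms' switching rates reverses every sign. Equal switching does not guarantee zero bias: with 10% switched in each arm at 60% risk in saline and 35% in acetate Ringer's, the retained rates are 0.322 and 0.350, a difference of 2.8 points.

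**Switching that produces a 1.5-point shift.** Setting (0.35 − s·r)/(1 − s) = 0.335 gives s = 0.015/(r − 0.335). For r = 50%, 60% and 70%, s = 9.1%, 5.7% and 4.1%, or about 14, 9 and 6 of 156 saline patients.

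**Error rate.** With 10% of saline and no acetate Ringer's patients dropped, 140.4 and 156 patients remain. Let d be the spurious difference and SE = √[p₁(1 − p₁)/140.4 + 0.35·0.65/156]. The two-sided 5% error is then Φ(d/SE − 1.96) + Φ(−d/SE − 1.96). For r = 70%, d/SE = 0.0389/0.0546 = 0.71 and the error is 0.11. For r = 50%, d/SE = 0.0167/0.0551 = 0.30 and the error is 0.06.

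**With every patient kept in the assigned arm.** Under the same assumptions both expected rates stay at 35%, the difference is zero, and the error rate stays at 5% for any s and r.

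**The case against.** The strongest reply is that the rule treats both arms alike, the article reports no switching rate, and it says itself that which fluid is better remains controversial. This stands in part. A reader might infer that the rule strips high-risk patients out of the saline arm, but the document does not show that. The trigger is a judged effect of the fluid, not a high baseline risk, and no laboratory value or other criterion is named for switching. Open label and the saline hypothesis make imbalance plausible, not established.

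A reader might also infer that patients with suspected harm vanish from the safety data. The text does not support that. The same section has adverse events recorded over the whole 28 days, reported to the monitoring board and tabulated at the end, with no exemption for switched patients. What is unclear is whether the final analysis includes the between-arm adverse event comparison.

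On timing, the fluid follows the calendar month, so the other crystalloid could be chosen at the outset as well as later. Reference to an assigned fluid makes exclusion after assignment the natural reading. Either way the choice is made knowing the arm.

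Finally, the sample size is framed as noninferiority, although the Objectives speak of superiority. Crossover dilutes differences under intention-to-treat and can make noninferiority easier to conclude, so intention-to-treat alone is not automatically the cautious choice. This objection stands and changes the fix. It does not rescue an unlabelled exclusion from the primary analysis.

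An unseen statistical analysis plan would not settle the matter, because the article does not leave the analysis set open. It states two incompatible rules.

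**Conclusion.** The contradiction is real and rests on the text alone: the exclusion cannot coexist with an intention-to-treat primary analysis, and it is made with knowledge of the arm for a reason that may be related to outcome. It needs correcting because it decides who enters the primary comparison.

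The size is conditional. Under the stated assumptions, saline-only switching of 10% at 50% to 70% risk produces a spurious 1.7 to 3.9 points, above the 1.5% limit, and raises a 5% two-sided error to about 6% to 11%. The bias is zero if switching and risk are equal across arms or if switched risk is about 35%. If higher-risk patients leave saline more often, saline is flattered. If they leave acetate Ringer's more often, that arm is flattered. The document does not fix which, so no claim that the trial favours one fluid is warranted.

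**What to change.** 1. Delete the exclusion sentence under Risk evaluation and adverse events. State that every assigned patient is followed to day 28 and analysed for MAKE28 in the assigned arm, whatever fluid was given.
2. Record each switch with its date and reason, and report switches by arm.
3. Keep the analysis that leaves out switched patients as a labelled supportive per-protocol analysis. If a noninferiority conclusion is drawn, report it beside the intention-to-treat result.
4. State whether switched patients are included in the between-arm adverse event comparison.

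The cost is a few sentences, fields on the case report form for the switch, and complete 28-day outcomes for switched patients. The last should add little work, since the data come from hospital records. The statistical price is some dilution from crossover, which the choice of intention-to-treat already accepts and which the supportive analysis helps to show. The change concerns the analysis set only and leaves the clinician's freedom to switch as it is.
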